**Fig. 2 Fig2:**
[figure not shown]
Schedule of enrollment, interventions, and assessments

The study will be presented at the time of an interview with the nursing personnel from the department assigned to the CEOPS study, in the presence of the doctor from the department, and a family member/friend likely to participate in the optimized follow up will be identified. The family member/friend is chosen on a voluntary basis, on the ability to understand and follow the different aspects of the recommendations, and on the proximity to the patient. After a period of consideration, the patient and the caregiving family member/friend will give their consent to participate in the study. Patients will be randomized into two groups, “optimized follow up” or “typical follow up.” Before being discharged, the two training sessions for the patient and the caregiving family member/friend will be given by the nursing personnel assigned to the CEOPS study. A letter of information will be sent to the attending physician and, possibly, to the other specialist physicians involved in the patient’s management (cardiologist, diabetologist, etc.). Before being discharged, blood pressure, the abdominal perimeter, glycosylated hemoglobin, plasma concentrations of the various lipids, coagulation parameters, the Rankin score, the quality of life scale and the Montreal Cognitive Assessment (MoCA) scale will be measured. The treatment upon discharge will be assembled.

In both groups, the patient and the family member/friend involved in the CEOPS study will be asked to fill out a follow-up notebook, where the following are to be noted: monitoring of blood pressure and various examinations performed, all the para-clinical examinations and consultations the patient has had, the adverse effects observed and the inter-current events. At each consultation, a report will be sent to the attending physician to keep the physician informed of the conclusions of the medical consultation. The nursing personnel assigned to the CEOPS study can at any time call on the physician in the department handling the patient’s follow up to inform the attending physician of the need for a change in treatment if it is found that the risk factors are not being properly monitored. One last information session will provide encouragement to the family member/friend to continue to be involved in the patient’s follow up in order to continue optimal monitoring of the risk factors and the treatment.

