### Primary outcome

Systolic and diastolic blood pressure will be measured at the 6-month, 1-year and 2-year visits, by a nurse blinded to the randomization. The main assessment criterion will be systolic blood pressure measured after the first year of follow up, offering a compromise between the feedback from 1 year, allowing long-term evaluation of the benefit of the optimized follow up by the pair and minimizing the risk of losing track, in the case of an evaluation after 2 years. Blood pressure will be measured by nursing personnel who do not know the group into which the patient has been randomized.

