### Sample size consideration

A population of 410 patients (205 in each arm) will be included in the study. The number of subjects necessary was calculated to show a difference in systolic blood pressure of 5 mmHg between the group with optimized follow up and the group with typical follow up, with an alpha risk of 5% and a beta risk of 20%. The variance in systolic blood pressure (18 mmHg) was calculated in the first 45 patients included in the study, in whom mean systolic blood pressure was 139.9 mmHg. The choice of the expected difference was justified by three reasons. First, there is a link between increase in blood pressure and the risk of stroke. Second, the Prediva study showed recently that a 2-mmHg decrease in blood pressure was unable to impact cognitive morbidity in the general population [32]. Third, with a 5-mmHg decrease in blood pressure, mean blood pressure should reach 135 mmHg, a level that is recommended in the guidelines and is in good accordance with a previous study [28].

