### Analysis strategy

Data will be analyzed by an analysis committee that will be blind to the groups studied, which will be called Groups A and B during the analysis. The assessment criteria will be expressed as quantitative values (mean and standard deviation) or as qualitative values (percentage). The variables expressed quantitatively will be blood pressure (systolic, diastolic, mean), glycosylated hemoglobin concentration, concentration of the various lipid parameters and scores on different scales (Rankin, MoCA, EQ-5D). The variables expressed qualitatively will be mortality rate, percentage of patients having another stroke, percentage of patients having blood pressure below the limit set by international guidelines, percentage of patients with normal glycosylated hemoglobin, percentage of patients with LDL cholesterol below 1 g/L and percentage of patients having a cognitive disorder (MoCA score <26). Quantitative data will be compared between the two groups using analysis of variance, with post-hoc analysis using Fisher’s least significant difference test in Prism (PLSD). Qualitative data will be compared between the two groups based on the chi-squared test and calculation of odds ratios. Sub-group analyses will be planned secondarily, depending on the cause of the stroke or depending on the patient’s cognitive state.

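### The two-group ANOVA named for 12-month systolic pressure makes no use of the pre-discharge or 6-month readings, so it can be biased if loss depends on earlier pressure differently by arm

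*Protocol article*

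**What the plan says.** All references are to the protocol article.

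- **Endpoint** (Primary outcome): "The main assessment criterion will be systolic blood pressure measured after the first year of follow up". One year was preferred to two partly for "minimizing the risk of losing track, in the case of an evaluation after 2 years".
- **Readings collected** (Primary outcome): "Systolic and diastolic blood pressure will be measured at the 6-month, 1-year and 2-year visits, by a nurse blinded to the randomization". Pressure is also taken at the end of the hospital stay (Procedure, text after Fig. 2): "Before being discharged, blood pressure, the abdominal perimeter, glycosylated hemoglobin" and other measures are listed there.
- **Method** (Analysis strategy): "Quantitative data will be compared between the two groups using analysis of variance". Systolic pressure is among the variables covered. No visit term, repeated-measures term or covariate is named.
- **Contact by arm**: the optimized arm has scheduled nurse calls between visits and can reach the nurse by telephone or email (Procedure for optimized follow up). The typical arm is followed by its own physician, with study consultations at 6 months, 1 year and 2 years (Procedure for typical follow up).
- **Size** (Sample size consideration): "A population of 410 patients (205 in each arm) will be included in the study", "calculated to show a difference in systolic blood pressure of 5 mmHg".

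**The concern.** A two-group analysis of variance of a one-visit endpoint has one observation per patient. Applied as written and without imputation, it takes nothing from a patient who was measured at discharge and at 6 months but missed month 12, although the same blinded measurement was made at month 6.

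The completers' comparison is safe if absence at month 12 is unrelated to pressure, or related to it in the same way and at the same rate in both arms. Here the arms differ by design in how closely patients are followed between visits, so a difference in who is lost is plausible. If typical-arm patients with high 6-month pressure stop attending, the typical-arm mean at month 12 comes out too low and the programme looks weaker than it is. If the selection is in the optimized arm instead, the programme looks stronger. The earlier readings carry information that could reduce this exposure, and the named method does not use it.

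**Working it through.** **1. The plan's own figure.** Inputs from Sample size consideration: difference 5 mmHg, alpha 5% (taken as two-sided), power 80%, spread 18 mmHg (used as an SD, the only reading that reproduces the total).

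n per arm = 2 × (1.960 + 0.842)² × 18² / 5² = 203.4, rounded up to 204, or 408 in total. The article states 205 and 410, so the figure reproduces. At 205 per arm, SE = 18 × √(2/205) = 1.78 mmHg and power is 80.3%.

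**2. When a completers' comparison is biased.** If loss after month 6 depends only on 6-month pressure, and the two readings have equal SD and correlation ρ, the completers' 12-month mean in an arm is off by

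ρ × (completers' 6-month mean − 6-month mean of all patients in that arm).

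The bias in the arm difference is the difference between the two arms' errors. It is zero when they are equal.

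**3. Size.** The documents supply neither a loss rate nor a correlation, so every input beyond the 5 mmHg and the SD is an assumption:
- true difference 5 mmHg at both 6 and 12 months;
- ρ = 0.4 or 0.6;
- loss 10-20% per arm, all after month 6;
- where loss is selective, log-odds of loss rising 0.7 per SD of 6-month pressure (odds × 2.0); in the last row the optimized arm's slope is −0.7.

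Simulation with 1,000,000 patients per arm (simulation error about 0.03 mmHg), optimized minus typical, mmHg:

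| Loss pattern | Loss typical/optimized | Completers, ρ = 0.4 | Completers, ρ = 0.6 | Likelihood estimate using month 6 (ρ = 0.4; 0.6) |
|---|---|---|---|---|
| Random | 15%/15% | −4.98 | −5.00 | −4.98; −5.01 |
| Random | 20%/10% | −4.98 | −5.04 | −4.98; −5.05 |
| Same selection in both arms | 15%/15% | −4.97 | −5.02 | −4.97; −5.02 |
| Same selection, unequal rates | 20%/10% | −4.54 | −4.29 | −5.00; −4.96 |
| Selective in typical arm only | 15%/15% | −4.26 | −3.93 | −4.97; −4.99 |
| Selective in typical arm only | 20%/10% | −4.07 | −3.57 | −5.01; −4.98 |
| Opposite selection | 15%/15% | −3.61 | −2.87 | −5.03; −5.01 |

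The first three rows show no bias. Unequal or one-sided selection gives 5 − 4.54 = 0.46 up to 5 − 3.57 = 1.43 mmHg. Opposite selection, the extreme case, gives 1.39 to 2.13 mmHg.

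Check against step 2, typical arm only at 15%/15%: 0.74 / (0.4 × 18) = 0.10 and 1.07 / (0.6 × 18) = 0.10. Both correlations imply the same shift of about 0.10 SD (1.8 mmHg) in the completers' 6-month mean, as they should.

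**4. Effect on power in that scenario.** With 15% lost, 205 × 0.85 = 174.25 per arm and SE = 18 × √(2/174.25) = 1.93 mmHg. Power for 5 mmHg is 73.7%; this fall from 80.3% comes from numbers alone. An expected difference of 4.26 gives 4.26/1.93 − 1.96 = 0.25, about 60%. One of 3.93 gives 3.93/1.93 − 1.96 = 0.08, about 53%. Only this second fall comes from bias.

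**The case against.** The Analysis strategy sentence is generic. It covers pressure, glycosylated hemoglobin, lipids and scales together, and adds a post-hoc test that is redundant for two groups at one visit. A reader might infer that patients without a 12-month reading are to be discarded. The article does not say so: it states no analysis set, no completers' rule and no missing-data rule. These are commonly left to the full protocol or analysis plan, and their absence is not the point made here.

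A reader might also infer that the authors forecast loss at 12 months. They do not. Loss is mentioned as a reason to prefer one year to two, and no rate is given. Other features work against loss: both arms have study consultations at the same three times, and both require a committed caregiver.

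The numbers also favour the remedy by construction. Drop-out was simulated from the 6-month value alone, which is the mechanism that a likelihood estimate corrects. Loss depending on the unseen 12-month pressure, or occurring before month 6, was not simulated.

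All of this stands and limits the claim. It does not remove it. The endpoint is fixed at one visit and the method is named, and that method as worded makes no use of earlier readings. An analysis plan that follows the article inherits the exposure; one that does not would be changing the published method.

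**Conclusion.** The point holds conditionally. The stated method leaves the pre-discharge and 6-month pressures unused. If it is run on patients with a 12-month reading, it can be biased when loss depends on earlier pressure differently by arm. The contrast in nurse contact makes that plausible, and nothing in the article shows that it will happen.

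Under the assumptions listed, bias runs from zero to roughly 0.5-1.4 mmHg of the 5 mmHg target under unequal or one-sided selection. The scenarios run all shrink the difference; selection confined to the optimized arm would enlarge it. The stronger statement that the primary difference is biased is not supported, because bias needs loss that is both related to pressure and different between arms, and the documents give no figure for either.

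**What to change.** Make the primary analysis a likelihood-based mixed model for repeated measures of systolic pressure, with arm, visit, arm-by-visit and an unstructured covariance. Include the pre-discharge value and all scheduled follow-up readings available at the time of analysis. Name the month-12 arm difference as the single primary contrast and keep the 12-month-only comparison as a sensitivity analysis.

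Two details need wording:
- **Pre-discharge value.** As a covariate it gives nothing for patients with no follow-up reading; as a response it keeps them in the model. The article does not make clear whether it is taken before allocation and before the training sessions. Settle that before assuming equal arm means at that time.
- **Assumption.** State that the model assumes missing at random given the observed readings, and that it does not correct loss depending on unobserved pressure.

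The cost is analysis wording and slightly more analysis work, settled before the coded groups are compared. The endpoint, visits and data collection do not change.

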During the first session, an explanatory brochure made within the context of the CEOPS study will be given to the patient and the family member/friend involved in the follow up. The second session will be to evaluate full understanding of the information given in the first session. Once the patient leaves the hospital, and after informing the attending physician, a monthly telephone interview for the first 6 months will make it possible to answer the questions from the patient and the family member/friend; explain again, if necessary, the lifestyle rules or, if necessary, the procedure for monitoring the risk factors; and identify a possible inter-current event requiring contact between the medical team from the vascular neurology department and the attending physician. In the case of a particular difficulty in the follow up, direct contact at the department or at home will be scheduled. In the sixth month, the patient will be seen in a medical consultation in the presence of the caregiving family member/friend, at which time the assessment criteria and another training session by the caregiving nursing personnel will be evaluated. During the second 6-month follow up, telephone contacts will take place every 2 months, and another medical consultation will be scheduled at the end of the 6 months with the same objectives (assessment criteria, information session). During the second year of follow up, telephone contacts will take place every quarter, and a medical consultation will be scheduled at the end of the second year to evaluate the assessment criteria. Beyond regular contact, the patient or the family member/friend can, at their initiative, contact the nursing personnel involved in the study by telephone or email. The contact is essentially a phone-based contact or a direct contact during the visit to collect any information even if the patient decides to discontinue the protocol.

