#### Procedure for typical follow up

Before the patient is discharged, the doctor and the nursing personnel will explain to the patient, in the presence of the family member who has agreed to be the caregiver, the lifestyle measures (salt, diet low in fats and carbohydrates, physical exercise) and treatments prescribed (purpose of the various medications, monitoring, possible adverse effects), the advantages and methods of self-measurement of blood pressure and the methods for following up on blood sugar, in cases of diabetes mellitus, or the anticoagulant treatment. Follow up will only be done by the attending physician. Patients, in the presence of the family member/friend involved in the study, will be seen again in a medical consultation after 6 months, 1 year and 2 years, at which time the assessment criteria will be evaluated.

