### Secondary outcomes

Several secondary endpoints will be recorded at the different visits: glycosylated hemoglobin at 6 months, 1 year and 2 years to assess glucose metabolism; the plasma lipid parameters (total cholesterol, low-density lipoprotein (LDL) cholesterol, high-density lipoproteins (HDL) cholesterol and triglycerides); anticoagulant treatment monitoring, if relevant; waist circumference; therapeutic compliance (8-item Morisky scale); mortality; occurrence of a new stroke or myocardial infarction; and occurrence of adverse effects from medications (with validation by a regional drug monitoring center). Functional disability will be assessed by the Rankin score, cognitive state by the MoCA scale and quality of life by the Euroqol 5-Dimension (EQ-5D) questionnaire. The medico-economic impact will be assessed by a specific questionnaire filled out by the caregiver, with information on number of consultations (general practitioner, specialized consultations), home nurse time, physiotherapy consultation, number of para-clinical examinations, number of hospitalizations, professional inability, assignment of loss of autonomy (housekeeper, help with personal hygiene, medical device) and remote alarm. The analysis will be also based on an estimation of time spent by the caregiver (personal time, professional impact) and the impact on the caregiver’s own health status.

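### Deaths and recurrent strokes over 2 years are compared as crude percentages by chi-squared, which cannot use partial follow-up; if loss differs by arm, the comparison of these secondary outcomes is biased in a direction the article leaves open

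*Protocol article*

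**What the plan says.** All references are to the protocol article.

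- **Event outcomes.** Secondary outcomes lists "mortality; occurrence of a new stroke or myocardial infarction". Analysis strategy then sets the variable type: "The variables expressed qualitatively will be mortality rate, percentage of patients having another stroke".
- **Test for them.** "Qualitative data will be compared between the two groups based on the chi-squared test and calculation of odds ratios". No time-to-event method is named.
- **Rankin.** It is placed among the quantitative variables, under "scores on different scales (Rankin, MoCA, EQ-5D"), summarised by mean and standard deviation. The test is fixed too: "Quantitative data will be compared between the two groups using analysis of variance".
- **Follow-up.** Patients in the typical arm "will be seen again in a medical consultation after 6 months, 1 year and 2 years", and the optimized arm has consultations at the same times. Between visits, only the optimized arm has scheduled nurse calls.
- **Loss.** Primary outcome justifies the 1-year endpoint partly by "minimizing the risk of losing track, in the case of an evaluation after 2 years". No rate is given.
- **After discontinuation.** The intention "to collect any information even if the patient decides to discontinue the protocol" stands under the procedure for optimized follow up; the section on typical follow up has no matching sentence.

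**The concern.** The choice of method is stated, so it is not simply left to an analysis plan, and a plan that follows the article inherits it.

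Death and recurrence are counted over a 2-year window. A two-by-two table needs a yes or no for each patient in it. Someone last seen free of events at 8 months contributes 8 months of information that the table cannot hold: the patient is entered as a no for the full 2 years, or left out. Equal loss in both arms does little harm to the comparison. Unequal loss is another matter, and the design makes it plausible. In year 1 the optimized arm has 9 calls by the procedure section (6 monthly, then 3 two-monthly) or 12 by the Abstract, then quarterly calls. (The two schedules should be reconciled, but the point does not depend on which applies.) Outside the study visits, the typical arm is followed by the attending physician alone.

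What is at stake is the reading of the outcomes closest to the purpose given in the Discussion, which is to lower morbidity and mortality.

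Rankin raises a smaller question. It is a short ordered scale in patients selected for limited sequelae, and a mean treats its steps as equal. A patient who has died attends no visit and has no score unless a rule assigns one.

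**Working it through.** **The plan's own figure.** The article gives no event rate, loss rate or power for deaths, recurrence or Rankin, so there is nothing to reproduce for these outcomes. Its sample size does reproduce: 2 × (1.96 + 0.84)² × 18² / 5² gives 204 per arm with 18 mmHg taken as the standard deviation, and the t-based calculation gives 204.4, hence 205. That figure has no bearing on this point.

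**Inputs, all assumed.** True 2-year risk of recurrence 10% in both arms (no treatment effect). Loss over 2 years 10% in the optimized arm and 20% or 25% in the typical arm. Constant hazards, loss unrelated to risk, events before loss known, competing deaths ignored.

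**Formulae.** Event hazard λ = −ln(0.9)/2 = 0.0527 per year. Loss hazard μ = −ln(1 − loss)/2.

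- Event seen before loss: E = λ/(λ+μ) × (1 − exp(−2(λ+μ))).
- Followed to 2 years without event: C = 0.9 × (1 − loss).
- Lost patients counted as event-free: percentage = E.
- Lost patients without an event dropped: percentage = E/(E + C).

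| Loss | μ | E | C | Counted event-free | Dropped |
|---|---|---|---|---|---|
| 10% | 0.0527 | 0.0950 | 0.810 | 9.5% | 0.0950/0.9050 = 10.5% |
| 20% | 0.1116 | 0.0898 | 0.720 | 9.0% | 0.0898/0.8098 = 11.1% |
| 25% | 0.1438 | 0.0871 | 0.675 | 8.7% | 0.0871/0.7621 = 11.4% |

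The true figure is 10% throughout. Counting lost patients as event-free makes the better-followed arm look worse (9.5% versus 9.0-8.7%). Dropping them makes it look better (10.5% versus 11.1-11.4%).

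**Check with a different loss pattern.** With loss spread uniformly over 2 years, 5% versus 20%, and true risk between 5% and 15%, the odds ratio (optimized to typical, truth 1.00) is 1.09-1.10 if lost patients count as event-free and 0.91 if they are dropped. With 10% loss in both arms it stays at 1.00.

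**Size against sampling error.** On the event-free branch the gap is 0.5 to 0.8 points, or 1 to 2 patients per 205. The standard error of the difference is about √(2 × 0.0925 × 0.9075/205) = 2.9 points, so the expected shift in the test statistic is about 0.2 to 0.3. Two-sided type I error would move from 5% to between about 5.4% and 5.9%.

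**Rankin, on assumed figures.** With deaths of 3% versus 6% and a survivor mean of 1.5 in both arms, survivors alone show a difference of 0. Scoring death as 6 gives (0.97 × 1.5 + 0.03 × 6) − (0.94 × 1.5 + 0.06 × 6) = 1.635 − 1.770 = −0.135. With deaths of 5% versus 10%, and the prevented deaths surviving at about 4.5, the survivor mean in the optimized arm is (0.90 × 1.5 + 0.05 × 4.5)/0.95 = 1.66 against 1.50, so it looks worse; with death at 6 it is 1.88 against 1.95, so it looks better. The rule for deaths can decide the sign.

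**The case against.** **The stronger reading is not in the article.** A reader might infer that drop-outs are counted as event-free, that the better-followed arm will therefore show a false excess of events, and that deaths drop out of the Rankin comparison. Analysis strategy sets no denominator, no rule for lost patients and no Rankin value for deaths. Such rules are commonly left to a fuller document, and their absence is no fault of the article. This stands: neither the direction nor the handling can be asserted. What remains is that the named test offers no neutral option unless outcomes are complete.

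**Both arms share safeguards.** Consultations fall at the same times, a caregiver committed to 2 years is required before randomization, a notebook records intercurrent events in both groups, and assessors are blinded and separate from the study nurses. This stands as a reason to expect the difference in loss to be limited. Full ascertainment of vital status would remove the problem for mortality. It does not make unequal loss implausible, given how differently the arms are contacted.

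**Death before recurrence.** It is tempting to add that chi-squared wrongly treats a patient who dies as having avoided a second stroke. Cumulative incidence with death as a competing event counts that patient the same way, and with complete follow-up it equals the crude percentage. That complaint is not made here.

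**Rankin is partly preference.** A comparison of mean scores at about 205 per arm is a legitimate test, and death could be scored 6 in a mean as well. This largely stands, which is why Rankin is secondary.

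**Stakes.** The effect is small on assumed rates, and the outcomes are secondary. This stands.

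**Conclusion.** The point holds in a limited form. The article fixes a method for 2-year mortality and recurrence that cannot use partial follow-up. With incomplete and unequal follow-up, the comparison is biased in a direction that depends on a handling choice the article does not state. On the assumed inputs the distortion is under 1 percentage point, well inside sampling error. Event risk, loss rates and their difference by arm are all assumptions; with equal loss the bias in the comparison disappears.

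The documents do not support a claim that drop-outs will be scored as event-free, that deaths will be excluded from Rankin, or that either arm will be favoured. The primary analysis of systolic blood pressure at 1 year is untouched. The change is worth making because it is cheap and improves a method the article has already chosen.

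**What to change.** - **Mortality:** Kaplan-Meier curves by arm and a Cox hazard ratio with 95% confidence interval, censored at last contact.
- **New stroke, and new stroke or myocardial infarction:** cumulative incidence with death as a competing event, plus a hazard ratio with 95% confidence interval, censored at last contact.
- **Status measured at a visit** (blood pressure, LDL cholesterol or glycosylated hemoglobin at target, MoCA below 26): keep chi-squared or logistic analysis.
- **Rankin, secondarily:** a proportional-odds analysis with death scored 6, adjusted for the pre-discharge score, in place of the mean by ANOVA.

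The cost is wording in the analysis plan and recording of event and last-contact dates. Design, sample size and primary analysis do not change. Two assumptions come with it: censoring must be non-informative for the time-to-event estimates to be unbiased, and proportional odds must be checked for Rankin.
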